### Follow-up of vaccinated and unvaccinated participants

icddr,b field staff will follow up with vaccinated and unvaccinated study participants bi-weekly through mobile phone for the entire influenza season. During the follow-up, data will be recorded on health outcomes, including respiratory symptoms, influenza-like illness, hospitalization, and death. To minimize loss to follow-up, icddr,b field team will contact the cohort member at their convenience. icddr,b field team will use the alternative number collected during enrolment where they cannot reach their regular mobile phone number. At the end of one follow-up interview, the interviewee will be consulted about the convenient time of their upcoming follow-up date. After taking these approaches, if it is impossible to reach a cohort member for three follow-up schedules, he/she will be declared lost to follow-up case. For the loss to follow-up case, icddr,b field team will place notes on their data identification number. The study flow chart is shown in Fig. 2.

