### Study setting

We selected study hospitals considering several factors. Firstly, we will use the hospital-based influenza surveillance (HBIS) platform to conduct this study. We have chosen Rajshahi Medical College Hospital and Khulna Medical College Hospital for our study activities on high-risk groups’ vaccine acceptability and cost-effectiveness. We will enroll Severe acute respiratory illness (SARI) and influenza like illness (ILI) patients identified from the HBIS platform to meet our study objectives. We will also collect influenza virus test results from the HBIS platform and data on influenza illness episodes’ costs from the influenza-positive SARI and ILI patients. This approach will save influenza virus testing costs not allocated in the current study budget. Secondly, to assess the outcome of influenza vaccination, we plan to enroll patients from public tertiary-level hospitals (one treatment/vaccinated and the other control hospital) to minimize baseline differences between the treatment/vaccinated and control arm. Thirdly, we have chosen Ragib-Rabeya Medical College & Hospital to represent public and private healthcare facility cost differences while estimating the costs of influenza illness. A brief description of the study sites’ bed occupancy rate and average monthly admission are represented in Table 2 [29, 30].

**Table 2 Tab2:** Demographic characteristics of the study hospitals

Study sites	Bed occupancy rate (%)	Total no OPD visits	Total number of PNC visits	Total number of admission	Middle wealth quantile
Rajshahi Medical College Hospital	198.05	114,818	2,405	22,022	24.1%
Khulna Medical College Hospital	275.00	35,311	991	8,859	24.8%
Jalalabad Ragib-Rabeya Medical College & Hospital	NA	NA	NA	NA	15.8%

Source: Local health bulletin October 2022

OPD = outpatients care department; PNC = post-natal visit

Note: a bed occupancy rate greater than 100% indicates that these hospitals receive and care for more patients than their capacity

Study sites for influenza vaccine acceptability, health beliefs, barriers:

We will conduct a health belief model (HBM) survey in two conveniently selected hospitals:

Rajshahi Medical College Hospital, Rajshahi.Khulna Medical College Hospital, Khulna.

Study sites for influenza vaccination cost-effectiveness objective:

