### Data collection to determine vaccination cost-effectiveness

#### Vaccination campaign

To record health outcomes after influenza vaccination, in one of the two public tertiary-level study hospitals, we will conduct an influenza vaccination campaign before the influenza season, where the vaccine will be offered free of cost to high-risk patients, and in the second hospital, vaccination will not be offered. We will work with the hospital administration to set up a vaccination booth on the hospital premises. Vaccines will be made available at the vaccination booths. Posters and leaflets containing information on influenza vaccination will be displayed at the vaccination booths and key hospital locations with information on the vaccination. Inpatients and outpatients of all departments will be informed about the ongoing immunization campaign. Eligible patients will be offered to take the vaccine during the vaccination campaign. Benefits, significance, adverse effects, and how to manage them will be explained to the patients. Nurses/ Health Assistants (HA) will provide influenza vaccination throughout the campaigns. At 8 AM, the vaccination booth will open and close at 2 PM, six days a week throughout the campaign period. A vaccination card will be issued to the participants. All high-risk groups will get one dose of seasonal influenza vaccination (Quadrivalent), except children aged six months to 8 years, who will receive two doses four weeks apart [31, 32]. All vaccines will be the southern hemisphere vaccine as recommended by the WHO for Bangladesh. Regarding children, we will make phone follow-ups with the guardians of the children receiving the first dose to remind them about the second dose schedule, and it will be recorded in the vaccine card if the second dose is received. In order to ensure the availability and quality control of vaccines throughout the three-month campaign period, the research team at icddr,b will closely monitor the campaign. All vaccinated participants will receive notification regarding potential adverse events following immunization (AEFI) during the vaccination process. To document any untoward occurrences after Adverse Events Following Immunization (AEFI), we will adhere to the pre-existing surveillance mechanism implemented by the World Health Organization (WHO) and the Ministry of Health and Family Welfare (MoHFW) of the government of Bangladesh. During the vaccination campaign briefing session in each study hospital, participants will be informed about the process of reporting any Adverse Events Following Immunization (AEFI) within the hospital’s established surveillance system. Additionally, participants will be provided with the mobile number, as stated in the consent form, to report any such issues. Furthermore, during the vaccination campaign implementation, a representative from icddr,b will be assigned to each study hospital to oversee and monitor any adverse events following immunization (AEFI) in conjunction with the hospital’s existing surveillance system. If an Adverse Event Following Immunization (AEFI) case is identified, the personnel affiliated with icddr,b will promptly notify the Hospital Surveillance Officer (HSO), provide support to the HSO in completing the AEFI report form, and subsequently transmit it to the Expanded Programme on Immunization (EPI) headquarters via the Chief Health Officer.

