### The cost associated with influenza illness

For collecting data on costs associated with influenza illness, we will enroll high-risk individuals visiting study hospitals who will meet the SARI and ILI case definitions:

Severe acute respiratory illness (SARI): In the case of patients across all ages, the presence of a history of or a recorded temperature equal to or exceeding 38.0 °C and cough began during the last ten days and required hospitalization [47].

Influenza-like illness (ILI): Measured fever above ≥ 38.0 °C with cough having an onset within the last ten days [47].

We will collect data on the enrolled participants’ direct and indirect medical costs associated with influenza illness episodes. Cost breakdowns for influenza illness episodes are provided below.

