#### The sample size for the vaccine effectiveness objective

Our primary outcome for health outcome for vaccination is vaccine efficacy against influenza among high-risk group populations. Studies from neighboring countries found that ILI symptoms were 15.30% of children, 31.23% of adults with chronic illness, 10.97% of pregnant women, and 20% of the elderly [68–70]. A systematic review of seasonal influenza vaccine policy, use, and effectiveness also revealed that pooled vaccine effectiveness for high-risk groups in the tropics and subtropics ranged from 48 to 88% (10). We expect a similar vaccine efficacy between 50 and 81% for our study’s targeted high-risk group population. A 5% significance level, 80% power, design effect 1.2, and 10% non-response were used to calculate the required sample size to estimate vaccine effectiveness [65–67]. Table 5 represents the high-risk group’s estimated sample size for vaccine effectiveness.

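### Cohort influenza-like illness is open-label phone self-report with no described masking and no ILI definition fitted to the calls, so uneven ascertainment could bias vaccine effectiveness in either direction

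*Protocol article*

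**What the plan says.** **Allocation and counselling.** Under Vaccination campaign, one public hospital openly offers free vaccine and the other does not. At the campaign hospital, "Benefits, significance, adverse effects, and how to manage them will be explained to the patients"; posters, leaflets and a vaccination card go with it. The closing paragraph of that section says the second hospital enrols an unvaccinated cohort and runs no campaign.

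**Outcome collection.** Follow-up of vaccinated and unvaccinated participants states that "icddr,b field staff will follow up with vaccinated and unvaccinated study participants bi-weekly through mobile phone" throughout the season, and that "data will be recorded on health outcomes, including respiratory symptoms, influenza-like illness, hospitalization, and death". The schedule is the same for both arms. The section does not say who decides that an episode is ILI, by what rule, or whether the caller can see vaccination status.

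**ILI definition.** It appears only under The cost associated with influenza illness, for enrolling hospital patients into the cost survey: "Measured fever above ≥ 38.0 °C with cough having an onset within the last ten days".

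**Named outcome and testing.** The sample size section says "Our primary outcome for health outcome for vaccination is vaccine efficacy against influenza among high-risk group populations", but the event rates it uses are ILI symptom rates. Study setting takes virus results from the surveillance platform for patients whom that platform identifies, and adds: "This approach will save influenza virus testing costs not allocated in the current study budget". No swab or record check is described for a cohort member who reports illness by phone.

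**Estimator.** Vaccine efficacy estimation uses covariate-adjusted Poisson regression and sets effectiveness to (1 − RR) × 100.

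**The concern.** Mild respiratory illness is easy to mention or to leave out on the phone. People told that a vaccine protects them may report less of it; people alerted to adverse effects may report more. A caller who knows the status may probe differently. With no fixed rule for turning answers into ILI, such differences reach the event count.

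The effectiveness estimate serves the cost-effectiveness objective, whose results are meant to inform national policy. Participants cannot be blinded in this design. Standardising the questions and the case decision is therefore the main safeguard available, and it must be in place before the calls are made.

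**Working it through.** No stated figure in the plan is in dispute, so there is none to reproduce. Three checks apply.

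**1. Does the ILI definition fit the calls?** The onset window is ten days. Read as every two weeks, the call interval is 14 days. Illness starting 11 to 14 days before a call falls outside the window: 4 of 14 days, or 29% if onsets are spread evenly. The Abstract and Study design instead say monthly contact; over 30 days, 20 of 30 days (67%) would fall outside. Only a twice-weekly reading would cover every day. A window applied identically in both arms loses cases without necessarily biasing the ratio. The point is that the definition cannot be used unchanged, and the article does not say what replaces it.

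**2. How does uneven ascertainment enter the estimate?** Let s be the ratio of the recorded fraction of ILI, vaccinated to unvaccinated. Then RR observed = RR true × s, so

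apparent VE = 1 − (1 − true VE) × s.

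On the Poisson log scale the vaccination coefficient becomes log(RR true) + log(s). Only the sum is estimable. Age, sex, income and similar covariates do not separate the two terms, because s differs by vaccination status itself.

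The documents give no value for s; those below are assumptions. The true values 50% and 81% are the ends of the range in the sample size section.

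| True VE | s = 0.8 | s = 0.9 | s = 1.1 | s = 1.2 |
|---|---|---|---|---|
| 0% | 20% | 10% | −10% | −20% |
| 50% | 60% | 55% | 45% | 40% |
| 81% | 84.8% | 82.9% | 79.1% | 77.2% |

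**3. Would a small s matter at the planned sizes?** Inputs: the ILI rates in the sample size section (children 15.30%, pregnant women 10.97%, elderly 20%, chronic disease 31.23%); the Table 5 sizes for effectiveness (465, 756, 736, 610); design effect 1.2; non-response 10%. Effective size per arm is Table 5 × 0.9 / 1.2 if Table 5 is per arm, and half that if it counts both arms, which the article does not say. For children, 465 × 0.9 / 1.2 = 349, or 174. With true VE 0% and s = 0.9, the chance of a falsely significant benefit (two-sided 5% test, so nominally 2.5% in that direction) is:

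| Group | Table 5 = both arms | Table 5 = per arm |
|---|---|---|
| Children | 6.0% | 8.3% |
| Pregnant women | 6.3% | 8.8% |
| Elderly | 8.7% | 13.3% |
| Chronic disease | 10.9% | 17.7% |

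These figures show sensitivity to an assumed s. They are not estimates of the bias in this study.

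**The case against.** The strongest reply is that open self-report comes with an offer/no-offer design, that scripts and masking belong in a full protocol not shown here, and that every figure above restates an assumed s. Much of that stands: no wrong number is shown, and differential reporting is a risk, not a demonstrated fact. But the article does set out the follow-up procedure in some detail (mode, interval, alternative numbers, rule for loss to follow-up), and participant unblinding follows from the design whatever a fuller document adds.

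Some stronger inferences are tempting and not supported:

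- **That callers are known to be unblinded.** The follow-up section names whom they call, not what they see, and it refers to identification numbers. The article is silent.
- **That callers and participants together judge what counts as ILI.** Respiratory symptoms are recorded too, which is compatible with itemised questions.
- **That extra calls inflate illness in vaccinated children.** The article says "we will make phone follow-ups with the guardians of the children receiving the first dose", but these are second-dose reminders. Nothing says outcomes are recorded on them, and scheduled follow-up is equal in both arms.
- **That only soft outcomes are collected.** Hospitalization and death are recorded in both arms and are less open to this bias.
- **That the control cohort hears nothing about influenza vaccine.** The health belief survey, which covers perceived severity and vaccine benefits, runs at both hospitals. One sentence under Vaccination campaign also places campaign briefings at every study hospital, which contradicts the statement that the second has no campaign.

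It is also fair that masking callers leaves participant-side under-reporting untouched.

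**Conclusion.** The point holds as a design weakness that is cheap to reduce. ILI in the cohort rests on phone self-report in an open, hospital-allocated comparison, after campaign counselling tied to one hospital. No masking is described, and the only ILI definition was written for another purpose and does not fit the calls. Covariate adjustment cannot separate uneven ascertainment from vaccine effect.

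The bias could go either way and its size is unknown; a reporting ratio of 0.9 turning 0% into 10% is illustration only. A reader might conclude that effectiveness will be overstated; the documents do not support a direction. The conclusion assumes that no masking or cohort ILI rule exists in a fuller document, and that bi-weekly means about every 14 days.

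**What to change.** In Follow-up of vaccinated and unvaccinated participants:

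1. Have the existing callers work from lists pooled across both hospitals under study ID, with hospital and vaccination status hidden. Ask any dose or adverse-event items last.
2. Use identical fixed items in both arms (fever and whether it was measured, cough, onset date, care sought). Derive ILI by program from fever plus cough, with onset since the last call.
3. Report hospitalization, already collected, and medically attended ILI beside all ILI as less subjective outcomes. They support the main result and do not replace it: they are also phone-reported and will be fewer.
4. State that participant-side reporting bias remains, and bound it with RR observed / s over a range of s fixed in advance. A benefit stops being significant once s falls to the upper 95% limit of the RR.

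Two texts must be reconciled first: the campaign briefings at every study hospital against the second hospital having no campaign, and the follow-up interval, given as monthly in the Abstract and Study design but bi-weekly in the follow-up section and the Discussion.

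Cost: changes to the call sheet and script, with the same staff and the same number of calls. Downside: some callers will be unmasked by what participants say. Items 2 to 4 still work when that happens.

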### The cost associated with influenza illness

For collecting data on costs associated with influenza illness, we will enroll high-risk individuals visiting study hospitals who will meet the SARI and ILI case definitions:

Severe acute respiratory illness (SARI): In the case of patients across all ages, the presence of a history of or a recorded temperature equal to or exceeding 38.0 °C and cough began during the last ten days and required hospitalization [47].

Influenza-like illness (ILI): Measured fever above ≥ 38.0 °C with cough having an onset within the last ten days [47].

We will collect data on the enrolled participants’ direct and indirect medical costs associated with influenza illness episodes. Cost breakdowns for influenza illness episodes are provided below.

### Direct medical and non-medical costs for influenza illness episodes

Direct costs will consist of health care provider fees, hospital registration fees, bed rental, prescriptions, laboratory testing, transportation, and mobile phone calls. We will also record informal payments made during hospital visits. All medications, laboratory tests, registration, and room rental costs will also be included. We will also collect payment if patients visit a pharmacy or other clinics prior to hospitalization. The non-medical expenses for patients or caregivers include food, lodging, and transportation. Our field staff will collect data directly from patients and their families. Members of the participant’s family or the participants themselves will be able to determine the drugs and tests they received at no cost due to hospital subsidies and those for which they incurred personal expenses (out-of-pocket).

### Productivity loss or indirect cost

We will also collect data on participants’ or caregivers’, or family members’ lost productivity and indirect costs incurred during illness. We will record the number of workdays missed by participants’ family members, participants themselves, and caregivers due to sickness or family caregiving. We will exclude weekends and national holidays from our calculation. Every day missed due to illness or the need to care for sick family members will be considered a forfeited workday for hourly-wage workers and housewives. We will not consider the days missed due to decreased activity, such as a partial work day, absences from school, or fatalities caused by influenza. The number of productive days lost due to influenza-related fatalities will be estimated based on the baseline mortality rate. This will be multiplied by the median daily wage in Bangladesh, followed by an adjustment based on the prevailing unemployment rate in the country.

### Costs of durable equipment and other fixed costs

We will collect the primary data on the costs of the supplies and materials consumed (not purchased and stored) at the hospitals involved in diagnosing and treating influenza illness by department, ward, and service, for example, per unit cost and required units for blood drawn, x-ray, blood culture test, C-reactive protein, widal test, complete blood count, etc. We will also collect data related to health facility operating hours (working hours by ward and department), the ticket prices of different departments’ inpatient or outpatient units, and bed rent.

### Collating secondary data for estimating cost-effectiveness of vaccination

#### Disability-adjusted life year (DALY)

We will collect secondary data on disability-adjusted life years (DALY) from the WHO global health estimation [48]. We will utilize age, and symptoms-specific DALY estimates to determine the DALY associated with influenza-related health outcomes. Though QALY is widely used for hospital patients, due to the unavailability of publicly available QALY data related to influenza or influenza-like illnesses for LMICs, we have decided to use the WHO’s publicly available DALY estimates for our study. We will utilize the WHO-recommended information spreadsheet. The spreadsheet contains estimates for disability-adjusted life year (DALY), categorized by WHO region, cause, age, and sex. The term “regional classification” pertains to the World Health Organization’s regional groupings as of 2019, which aligns with the most up-to-date reference year for this Global Health Estimates revision. The compilation of these statistics was carried out by the Department of Data and Analytics at the World Health Organization (WHO) in partnership with various technical programs within the WHO. The cause-specific estimates may exhibit significant ranges of uncertainty depending on the data sources that are accessible [49, 50]. The WHO Department of Data and Analytics prepared these statistics in collaboration with WHO technical programs [51, 52]. The cause-specific estimates may exhibit significant ranges of uncertainty depending on the data sources that are accessible. Due to alterations in data and some methods, these estimates are not comparable to previously released WHO estimates. Similar literature has been identified about facility-based vaccination, wherein the DALY metric was employed to assess the cost-effectiveness of such programme [53, 54].

#### Data sources for estimating influenza-associated disease burden

To estimate the key parameters of influenza-associated disease burden, such as the number of outpatient visits, hospitalization, and deaths, we will collect data from secondary sources [17, 26, 31, 34, 35, 54–58]: Table 1 represents the assumption and secondary data sources by each target risk group.

#### Vaccine coverage

We will use secondary data for the input parameters relating to seasonal influenza vaccination coverage in Bangladesh [10, 59–61]. We will use our proposed study data on the number of targeted high-risk group individuals getting influenza vaccination during the immunization campaign to estimate vaccine coverage [62]. We will extract information on hospitals’ catchment areas’ population size from the Statistical Yearbook of Bangladesh 2020 [26].

#### Vaccine adverse event costs

Vaccine adverse event costs will be estimated for each targeted risk group. Using primary and secondary data, we will estimate the costs of influenza vaccination adverse events. We will use secondary data to estimate influenza vaccination rates and adverse events, whereas primary data will be used to determine the cost [34]. We will assume that patients who have a minor adverse event will seek medical care at an outpatient facility where they will receive consultation from a qualified physician. On the other hand, all patients who experience a severe adverse event will need hospitalization. The unit cost for minor adverse events will be determined by the price charged by the outpatient care department and the fee charged by the physician. Fees for outpatient care departments and healthcare professionals will be derived from primary data. Similarly, the estimation of the cost associated with a severe adverse event involves the calculation of inpatient care costs, which encompass both general ward facility fees and specialist fees. This estimation is derived by multiplying these costs by the length of the patient’s hospital stay. The average duration of hospital stay for influenza-associated illnesses will be collected from secondary data, and inpatient care daily costs will be collected from primary data [63].

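### Vaccine adverse events are costed with fees only and influenza episodes with a wider set of components; with no stated perspective, the two sides of the ICER do not match

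*Protocol article*

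**What the plan says.** For vaccine adverse events, the protocol article (Vaccine adverse event costs) fixes the unit costs. For minor events, "The unit cost for minor adverse events will be determined by the price charged by the outpatient care department and the fee charged by the" (the consulting doctor). For severe events it takes "inpatient care costs, which encompass both general ward facility fees and specialist fees" and multiplies them by the length of stay. It also assumes that "patients who have a minor adverse event will seek medical care at an outpatient facility".

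For influenza, three sections set a wider list:

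- Direct medical and non-medical costs for influenza illness episodes gives the main items: "Direct costs will consist of health care provider fees, hospital registration fees, bed rental, prescriptions, laboratory testing, transportation, and mobile phone calls". Informal payments and payments to pharmacies or clinics before admission are recorded too, and "The non-medical expenses for patients or caregivers include food, lodging, and transportation".
- Productivity loss or indirect cost: "We will record the number of workdays missed by participants’ family members, participants themselves, and caregivers due to sickness or family caregiving".
- Costs of durable equipment and other fixed costs: supplies and tests used at the hospital in diagnosing and treating influenza.

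Study design says that the direct and indirect influenza costs are collected for the cost-effectiveness objective. Cost-effectiveness estimation defines the ICER as incremental cost over incremental DALYs, and lists treatment cost and productivity loss averted among further outputs. It names no costing perspective and does not list the components of incremental cost.

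**The concern.** Vaccination averts some outpatient visits and admissions and causes others, and both enter the same incremental cost. If an averted visit is credited with medicines, tests, travel and lost work, and a caused visit is debited only with the facility price and the physician's fee, like is not compared with like. All the missing items are costs of zero or more, so leaving them out can only lower the cost charged to vaccination. The results are meant to inform national vaccination policy, so a reader should be able to see that caused and averted care were priced on one basis. The adverse-event section states its component list outright, so this is a stated rule and not detail left to a fuller document.

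**Working it through.** The document states no adverse-event rate, adverse-event cost or ICER, so there is no figure to reproduce. The check compares components and then illustrates scale.

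**Components side by side**

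| Item | Influenza episode | Adverse event |
|---|---|---|
| Physician or specialist fee | yes | yes |
| Facility price or bed | yes | yes |
| Medicines, laboratory tests | yes | no |
| Transport, phone calls | yes | no |
| Food, lodging | yes | no |
| Informal payments, earlier pharmacy or clinic payments | yes | no |
| Lost workdays (patient, caregiver, family) | yes | no |

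No section adds the missing items to adverse events.

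**Inputs from the document**

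- Background: USD 108 million / 25 million outpatients = USD 4.32 direct cost per outpatient.
- Background: USD 1.4 million / 30,592 = USD 45.76 per hospitalised patient.
- Background: 100–170 influenza outpatients per 1,000 population.
- The sample size for the vaccine effectiveness objective: expected efficacy 50–81%.

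**Assumptions, not in the document**

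- Minor-event rate m = 1%, 5% or 20%; severe-event rate 0.01%.
- Fees are a share f = 20%, 50% or 80% of full direct cost.
- An adverse-event visit or stay would have the same full direct cost as an influenza one. This is a yardstick only.

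**Averted direct outpatient cost per 1,000 vaccinated** = 1,000 × rate × efficacy × 4.32

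- Low: 1,000 × 0.100 × 0.50 × 4.32 = USD 216
- High: 1,000 × 0.170 × 0.81 × 4.32 = USD 595

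**Omitted direct cost per 1,000 vaccinated** = 1,000 × (m × 4.32 + 0.0001 × 45.76) × (1 − f)

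| m | f = 80% | f = 50% | f = 20% | as share of USD 595 to 216 |
|---|---|---|---|---|
| 1% | 9.6 | 23.9 | 38.2 | 2% to 18% |
| 5% | 44.1 | 110.3 | 176.5 | 7% to 82% |
| 20% | 173.7 | 434.3 | 694.9 | 29% to 322% |

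Severe events contribute at most 1,000 × 0.0001 × 45.76 × 0.8 = USD 3.7, so minor events dominate under these assumptions.

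The choice of disease risk does not narrow this. Take instead the ILI risks in the sample-size section (10.97–31.23%), one visit per case and 50% efficacy. Savings are 1,000 × 0.1097 × 0.5 × 4.32 = USD 237 to 1,000 × 0.3123 × 0.5 × 4.32 = USD 675. With m = 2–10% and f = 20–50%, minor events alone omit 1,000 × 0.02 × 4.32 × 0.5 = USD 43 to 1,000 × 0.10 × 4.32 × 0.8 = USD 346. That is 43/675 = 6% to 346/237 = 146%.

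**The opposing assumption.** Expected minor-event cost per vaccinee is m × q × c, where q is the share of minor events that lead to a visit and c is the unit cost. The plan uses q = 1 and c = f × 4.32. Full costing uses the true q and c = 4.32. The two agree when q = f. With fees at 20–50% of full cost, the plan's total is therefore already right if 20–50% of minor events lead to a visit, and too high if fewer do.

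**The case against.** The strongest objection is about net direction. A reader might infer that the ICER as planned is biased towards cost-effectiveness. The document does not support that: the assumption that minor events lead to a consultation raises the number of costed visits and can offset, or outweigh, the low unit cost. This stands, and limits the point to the component mismatch with other things equal.

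A reader might also infer a definite multiple, such as a 2- to 5-fold understatement. That is only an assumed fee share of 20–50% turned upside down (1/0.5 to 1/0.2); a share of 80% gives 1.25. The comparison above also leaves out averted admissions and productivity losses, and does not set the omission against programme cost or the three-times-GDP threshold. No changed conclusion is shown. This stands too.

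Nor are all indirect costs of influenza counted: "We will not consider the days missed due to decreased activity, such as a partial work day, absences from school, or fatalities caused by influenza".

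What enters the ICER numerator is partly inferred. The plan relies on the built-in formulas of a spreadsheet tool, and productivity loss averted appears as a separate output. Under a payer perspective, lost work and patients' travel and food would drop out on both sides. Medicines and tests would still be unequal, so the mismatch narrows but does not vanish.

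Finally, the cost survey enrols ILI and SARI patients. Copying their full episode cost to an adverse event would import influenza-specific tests and payments for earlier care. This is right, and it shapes the fix.

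**Conclusion.** The mismatch is real. Adverse events are costed with facility and physician fees, influenza care with several further categories, and nothing in the document explains why. Taken alone, it understates the cost added by vaccination relative to the cost averted, and so moves the ICER in favour of vaccination. That direction assumes that the wider influenza costs enter the numerator, as Study design and Cost-effectiveness estimation suggest.

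Its size is undetermined: negligible if minor events are rare or fees make up most of the cost, and comparable with averted direct outpatient cost if events are common and fees are a small part. The planned probabilistic sensitivity analysis addresses parameter precision; varying a fee-only unit cost does not by itself restore missing categories.

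**What to change.** State one costing perspective under Cost-effectiveness estimation and apply the same cost categories to both sides of the ICER. Under Vaccine adverse event costs:

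- Add medicines and tests per outpatient visit and per inpatient day. Under a societal perspective, add transport, food and lost workdays as well.
- Use the unit costs that the cost survey already collects. Do not carry over influenza-specific test quantities or payments for earlier care: the perspective and categories should match, not the influenza resource use.
- Where adverse-event resource use is unknown, vary it in the sensitivity analysis from fee-only up to the full ILI per-visit or SARI per-day cost.

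The cost is a little more analysis and, other things equal, a slightly less favourable ICER. No new unit-cost data are needed.
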